Round 2 of data collection, or post-intervention assessment, will occur 4 weeks after the introduction of the intervention.

CPV scores will be used to compare baseline practice with practice post-intervention in the 3 different physician groups/arms.

This study will test the following hypotheses:

1. Clinical practice, specifically decisions around treatment of individuals with disorders of postnatal development including DD, ASD, and ID will vary widely among all physician types. This documentation of variation in practice will demonstrate the need for a new diagnostic service that FirstStepDx PLUS and NextStepDx PLUS would fulfill.
2. FirstStepDx PLUS and NextStepDx PLUS will improve the quality and appropriateness of care and therapeutic plans, as measured by the number of physicians that correctly act on the results of the assay.

This hypothesis will be tested through total of 9 CPVs consisting of 3 CPVs cases for each of 3 case archetypes as follows.

- Case A: Patients who are currently undiagnosed and for whom FirstStepDx PLUS or would initiate appropriate therapy
- Case B: Patients who are wrongly—or incompletely—diagnosed and for whom FirstStepDx PLUS would change therapy (i.e., terminate inappropriate or unnecessary therapy and initiate appropriate therapy)
- Case C: Patients who are undiagnosed by FirstStepDx PLUS testing and for whom NextStepDx PLUS testing would initiate appropriate therapy and/or earlier intervention will result in better outcomes

The CPVs™ will be randomly assigned to physicians for each to complete 3 CPVs™ (one from each type). Each of the CPVs™ will be scored by physicians for changes in clinical practice including treatment changes, frequency of follow up, laboratory tests and imaging studies ordered - see for scoring sheet.

|                   |                                                                                                                 |                       |
|-------------------|-----------------------------------------------------------------------------------------------------------------|-----------------------|
|                   | Clinical Study Protocol                                                                                  |                       |

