## 8. STATISTICAL ANALYSIS

### 8.1 Determination of Sample Size

The study is adequately powered to detect differences in clinical practice patterns as measured by the CPVs. A sample size of 75 in each arm provides over 80% power to detect an estimated 6-7% difference in practice with alpha=0.05.

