With longitudinal data we can estimate the effect of FirstStepDx PLUS testing or the sequential use of FirstStepDx PLUS and NextStepDx PLUS testing on our primary and secondary outcomes. After the round 2 data is collected, we will conduct the longitudinal analysis incorporating type of intervention, time (before versus after), and the primary predictor, the time by intervention interaction (to look for differential changes over time). This allows a difference in difference analysis comparing differences between groups before and after intervention to assess the effect of FirstStepDx PLUS testing or the sequential use of FirstStepDx PLUS and NextStepDx PLUS testing.

Primary Outcome Variable:

- Quality of care (CPV® diagnosis/treatment score)

Secondary Outcome Variables:

- Use of appropriate therapy
- Utilization counts of laboratory tests and imaging studies ordered
- Overall CPV score

We will control for all potential confounders, including:

- Age
- Gender

|                   |                                                                                                                 |                       |
|-------------------|-----------------------------------------------------------------------------------------------------------------|-----------------------|
|                   | Clinical Study Protocol                                                                                  |                       |
|                   | Title: Establishing the Clinical Utility (ECU) of First Step Dx PLUS and NextStep Dx PLUS |                       |
| Supersedes: Rev B | Document Number: Rev C                                                                                          |                       |
|                   | Effective Date: 11JUNE14                                                                                        | Page: 17 of 20 |

- Number of years since fellowship
- Awareness of FirstStepDx PLUS and/or NextStepDx PLUS
- Practice location
- Type of location (urban/suburban vs. rural)
- Number of patients seen per week and number of DD/ID patients seen per week
- Number of physicians in practice
- Single or multispecialty practice
- Practice ownership (e.g. physician-physician group, community health center, etc)

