- Avg. type of coverage of patients (Medicare, Medicaid, commercial, etc)

We will model CPV™ score as a continuous outcome variable in a multiple linear regression model, which controls for all potential confounders listed above. Our regression model is as follows, where CPV™ is the score for each physician, INTERV indicates type of intervention group and TIME indicates time period (pre and post-intervention).

$Y_{it}$  = CPVscore at time  $t$ , physician  $i$

$Y_{it} \sim Normal(\mu_{ijt}, \sigma_e^2)$

$\mu_{it} = \beta_0 + \beta_1 TIME + \beta_2 INTERV + \beta_3 TIME \times INTERV + \text{control variables}$

For binary outcome variables, for example use of biologic therapy, we will use a logistic regression model. Our regression is as follows, where INTERV indicates type of intervention group and TIME indicates time period (pre and post-intervention). For outcomes with a Poisson distribution, the distributional assumption would be changed from Bernoulli to Poisson and the link would be changed from logit to log. Otherwise, the basic modeling and analysis strategy will remain the same.

$Y_{it}$  = appropriate therapy  $t$ , physician  $i$

$p_{it}$  = probability of an outcome for time  $t$ , physician  $i$

$\text{logit}(E[Y_{it}]) = \beta_0 + \beta_1 TIME + \beta_2 INTERV + \beta_3 TIME \times INTERV + \text{control variables}$

For count outcome variables such as number of follow-up visits we will use log linear regression (i.e., using a log link in the analysis). Cluster re-sampled bootstrapping will be used to check model distributional assumptions.

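### The primary regression has no term for the physician, so the standard error of the time-by-intervention effect is too large and power is lost

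*Protocol*

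**What the plan says.** Protocol Section 2.2 sets up the repeated measurement: "CPV scores will be used to compare baseline practice with practice post-intervention in the 3 different physician groups/arms". Section 8.2, Longitudinal Data Analysis, then names the effect of interest as "the primary predictor, the time by intervention interaction (to look for differential changes over time").

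The same section gives the primary model explicitly. The CPV result is treated as a "score as a continuous outcome variable in a multiple linear regression model, which controls for all potential confounders listed above". The outcome is defined as "CPVscore at time" t for physician i, with distribution "Y_{it} \sim Normal(\mu_{ijt}, \sigma_e^2"). The mean contains an intercept, TIME, INTERV, their product and control variables. The control list consists of physician and practice characteristics; it contains neither a physician effect nor the baseline score. The logistic and log-linear models for the secondary outcomes follow the same pattern.

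Clustering appears once, at the end of the section: "Cluster re-sampled bootstrapping will be used to check model distributional assumptions".

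On size, Section 8.1 states: "A sample size of 75 in each arm provides over 80% power to detect an estimated 6-7% difference in practice with alpha=0.05". Neither Section 8.1 nor the synopsis gives an SD or a pre/post correlation.

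**The concern.** The primary effect is a difference in differences: the pre-to-post change in an intervention arm minus the change in the control arm. Its precision comes from scoring the same physician twice, because stable differences between physicians cancel in the change. A regression with a single independent error per row does not use this. It counts stable between-physician variation as noise in the change, so the model-based standard error is right only if the residual correlation between a physician's two scores is zero. That is unlikely for the same person tested twice a few weeks apart with the same kind of instrument.

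At stake are the p-value and confidence interval of the primary comparison. A real effect of the planned size could be reported as non-significant because of the error model alone.

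**Working it through.** **Inputs.** From the protocol: 75 physicians per arm, three arms, two-sided alpha 0.05, a difference of 6 to 7 points, power stated as over 80% (Sections 8.1 and 8.2, synopsis). Assumed, because the protocol gives no values: per-round SD s (residual, after covariates) and residual pre/post correlation rho of 0.3, 0.5 or 0.7.

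**Step 1: the stated power.** It cannot be reproduced without an SD. For a simple comparison of two means, 80% power needs difference / (s x sqrt(2/75)) = 1.96 + 0.84 = 2.80.
- 6 points: s = 6 / (2.80 x 0.163) = 13.1.
- 7 points: s = 7 / (2.80 x 0.163) = 15.3.

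These are the largest SDs consistent with the statement, if a simple two-group comparison was behind it.

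**Step 2: variance of the TIME x INTERV estimate (one intervention arm against control).**
- Assumed by the written model: 4s²/n.
- True, with correlation rho: 4s²(1 - rho)/n.
- Ratio of standard errors, written to true: 1/sqrt(1 - rho).

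**Step 3: consequences at s = 13.1, n = 75, 6-point effect.** The written standard error is 13.1 x sqrt(4/75) = 3.03 at every rho. The true size of the nominal 5% test is 2 x [1 - Phi(1.96 x ratio)]. Power as written is Phi(6/SE_true - 1.96 x ratio); power with pairing modelled is Phi(6/SE_true - 1.96).

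| rho | True SE | SE ratio | Actual size of 5% test | Power as written | Power, pairing modelled |
|---|---|---|---|---|---|
| 0 | 3.03 | 1.00 | 5.0% | 51% | 51% |
| 0.3 | 2.53 | 1.20 | 1.9% | 51% | 66% |
| 0.5 | 2.14 | 1.41 | 0.6% | 51% | 80% |
| 0.7 | 1.66 | 1.83 | 0.03% | 52% | 95% |

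Power depends only on the effect divided by the SD, so 7 points with SD 15.3 gives the same figures. For 7 points with SD 13.1, power at the three non-zero correlations is 66%, 69% and 74% as written, against 79%, 91% and 99%.

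**Step 4: SD at which the written model reaches 80%.** Taking the model's own standard error at face value (rho = 0), s = difference / (2.80 x sqrt(4/75)): 6 / (2.80 x 0.231) = 9.3 for 6 points, and 10.8 for 7 points.

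**Step 5: simulation.** 225 physicians, two rounds, SD 13.1, no covariates, 5,000 runs per correlation. At rho 0.3, 0.5 and 0.7 the written regression rejected a true null in 1.7%, 0.5% and 0.04% of runs; a change-score analysis rejected in 5.0%, 4.7% and 4.7%. Power for 6 points was 51% at all three correlations, against 65%, 80% and 95%. This agrees with the formulas.

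**The case against.** **The bootstrap already handles clustering.** Resampling whole physicians would give a valid standard error, and the sentence shows that the authors had clustering in mind. But the protocol uses the bootstrap only as a check. It does not name the cluster unit, say what follows if the check disagrees, or make the bootstrap the source of the interval or p-value.

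**The error structure belongs in a statistical analysis plan, and the equations look abbreviated.** There are signs of shorthand: the mean carries an index j with no matching term, and a probability is defined but not used in the equation. Had the protocol said only that a longitudinal model would be used, there would be no finding. It instead writes out the model and its error distribution, and an analysis that follows them inherits the fault.

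**The covariates absorb the correlation.** They remove only the part they explain. The rho that matters is what is left, and it may be lower than 0.7. This part of the objection stands: the factor 1.83 is the top of an assumed range.

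**The power loss rests on an assumed SD.** This also stands. An SD of 13.1 is back-solved from a two-group comparison that the protocol does not describe. With a per-round SD of 9.3 or less, the written model would reach 80% for 6 points.

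**A stronger reading: the test gives too many false positives.** A reader might infer this because Section 2.2 says that vignettes "will be randomly assigned to physicians for each to complete 3 CPVs", and several rows per physician treated as independent can make a standard error too small. The protocol does not support this reading. Section 8.2 defines one score per physician and time, and no vignette-level rows are stated. Even with three vignette rows per round, the direction is open. With within-round correlation w and between-round correlation b, true variance over assumed variance is 1 + 2w - 3b. At w = 0.5, b = 0.1 this is 1.7, and the actual error rate is about 13%. At w = 0.4, b = 0.3 it is 0.9, and the rate is about 3.9%.

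**Conclusion.** The point holds as an efficiency and reporting fault in the primary analysis as written. With one score per physician per round and positive residual correlation, the standard error of the interaction is overstated by 1/sqrt(1 - rho), the test is conservative and the intervals are too wide. The linear point estimate is unaffected, and a significant result from this model would not be undermined by this fault. The risk is a missed effect.

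The ratio of standard errors depends only on rho. The power figures also depend on the SD; since the protocol gives neither, they are illustrations and do not show that the study is underpowered. No size was calculated for the binary and count outcomes, where the same omission applies.

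**What to change.** In Protocol Section 8.2, Longitudinal Data Analysis, make one of these changes for the primary outcome:
- add a physician random intercept to the linear model;
- analyse each physician's change score by arm; or
- keep the regression for the estimate and take the primary confidence interval and p-value from a bootstrap that resamples whole physicians, or from standard errors clustered on physician.

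Account for clustering on physician in the logistic and log-linear models too, for example with GEE or cluster-robust standard errors. State that the analysis unit is one score per physician per round, and remove or define the index j.

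The cost is wording only; no new data or visits are needed. The choice should be fixed before round 2 data are analysed, because choosing the error structure afterwards could change the result.

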## 9. ADMINISTRATIVE CONSIDERATIONS

### 9.1 Study Compliance

The study will be conducted in compliance with this protocol, principles of ICH-6, GCP and the Declaration of Helsinki and all applicable national regulations governing clinical trials.

### 9.2 Protected Subject Health Information

A copy of the IRB approved informed consent may be audited. The investigator or designee **must** explain to each subject the purpose and nature of the study, the study procedures, the possible adverse effects and all other elements of consent as defined in 21CFR §50.

|                   |                                                                                                                 |                       |
|-------------------|-----------------------------------------------------------------------------------------------------------------|-----------------------|
|                   | Clinical Study Protocol                                                                                  |                       |
|                   | Title: Establishing the Clinical Utility (ECU) of First Step Dx PLUS and NextStep Dx PLUS |                       |
| Supersedes: Rev B | Document Number: Rev C                                                                                          |                       |
|                   | Effective Date: 11JUNE14                                                                                        | Page: 18 of 20 |

In accordance to individual local and national subject privacy regulations, the investigator or designee **must** explain to each subject prior to screening that for the evaluation of study results, the subject's protected information obtained during the study may be shared with Lineagen and its designees, regulatory agencies and IECs/IRBs. Lineagen will not use the subject's protected information or disclose it to a third party without applicable subject authorization. It is the investigator's or designee's responsibility to obtain a written permission to use protected information from each subject. Any data collected from a subject prior to withdrawal will not be used in the analysis of study results.

### 9.3 Retention of Records

The files of study subjects shall be retained in accordance with national legislation and the maximum period of time permitted by Lineagen. Lineagen will maintain records and documents on-site.

### 9.4 Confidentiality and Publication Policy

For publications, authorship will be determined according to the generally accepted principles of authorships and by mutual agreement.

|                   |                                                                                                                 |                       |
|-------------------|-----------------------------------------------------------------------------------------------------------------|-----------------------|
|                   | Clinical Study Protocol                                                                                  |                       |
|                   | Title: Establishing the Clinical Utility (ECU) of First Step Dx PLUS and NextStep Dx PLUS |                       |
| Supersedes: Rev B | Document Number: Rev C                                                                                          |                       |
|                   | Effective Date: 11JUNE14                                                                                        | Page: 19 of 20 |

